### Population

Patients will be eligible for inclusion if they are aged between 40 and 84 years inclusive (the age range recommended by the National Institute for Health and Care Excellence (NICE) for risk assessment^5^) with no previous diagnosis of CVD and at least one lipid result coded in the study period. The date of the first coded lipid result in the study period will be considered the index date. Patients must not have been prescribed a statin prior to the index date.

In order to maintain a stable cohort of practices, only THIN practices in which there are data available for the whole study period will be included. The study period will run from the beginning of 2012 to the end of 2016. Patients will be eligible for inclusion from the earliest of the following dates: study start date, acceptable mortality reporting date (which ensures that patient deaths and deregistrations are being recorded consistently^45^), Vision date plus 1 year, registration date plus 1 year (to ensure time for baseline data to be recorded), and age 40; until the earliest of the following dates: age 85, study end date, CVD diagnosis, other excluding diagnosis (as below), statin initiation or recording of a contraindication for the prescribing of statins. Patients will also be excluded if they left the database within 60 days of the index date.

Patients will be excluded if they had pre-existing CVD, were pregnant, had a contraindication to statin therapy (including allergies and drug interactions), were already being prescribed a statin (or other lipid-lowering therapy) or had ever been prescribed a statin in the past. Patients will be considered to have pre-existing CVD if they had a diagnosis of myocardial infarction, angina, peripheral vascular disease or stroke/transient ischaemic attack. Patients with type 1 diabetes mellitus, a diagnosis of chronic kidney disease stages 3–5 and patients diagnosed with or who were at risk of familial hypercholesterolaemia will also be excluded as statin use in these patients should not be based on CVD risk assessment. Patients at risk of familial hypercholesterolaemia will be defined as those with a total cholesterol of ≥9.0 mmol/L as this is the threshold for seeking specialist assessment defined in the NICE guidance.^5^

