## Study variables

### Exposure variables

The exposure of interest is the undertaking of lipid testing. Once a patient has their lipids recorded, this signifies that a clinician has made a decision about the significance of the lipid levels and will act on this. Individual patients may have multiple lipid results recorded over the study period. Assuming the exclusion criteria are not met, each lipid result will be considered as a new exposure so long as it is not within 60 days of the last recorded lipid level. The number of previous lipid results will be included in predictive modelling.

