### Outcome variables

The outcome will be the prescription of a statin within 60 days of a set of lipid results.

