## Analysis

Continuous variables will be categorised. Calculated and coded QRISK2 scores will be categorised according to risk bands (<10%, 10–14.9%, 15–19.9% and ≥20%). Age will be categorised into four groups (40–49, 50–59, 60–69 and ≥70). Total cholesterol (TC) will be categorised into three bands (<5.0, 5.0–6.9 and ≥7.0 mmol/L), and high-density lipoprotein (HDL) cholesterol into four bands (≤1.2, 1.3–1.4, 1.5–1.7 and ≥1.8 mmol/L) as these cut-offs have been used previously in the literature.^22^ Systolic blood pressure will be split into three groups corresponding to normotensive, stage 1 hypertension and stage 2 hypertension (<140, 140–159 and ≥160 mm Hg).^6^

The cohort will be described and prescribing rates and QRISK2 score trends will be established.

The primary analysis will consist of predictive modelling using multivariate logistic regression (variables summarised in table 1). Clustering of responses within individual general practitioner (GP) practices will be included in the model. Variation throughout the year due to the seasonality imposed by the Quality and Outcomes Framework (QOF) targets will be accounted for by adding the year quarter as a variable in the model. Assuming a minimum sample size for analysis of 10 per degree of freedom,^47^ and 57 degrees of freedom in the variables, a minimum sample of 570 patients with a lipid profile and subsequent statin initiation should easily be obtained.

**Table 1 BMJOPEN2016013120TB1:** Variables used in predictive modelling

Variable	Categories
Total cholesterol	<5.0, 5.0–6.9, ≥7.0
TC/HDL ratio	≤1.2, 1.3–1.4, 1.5–1.7, ≥1.8
Prior cholesterol measurements	0, 1–2, 3–4, ≥5
Calculated QRISK2	<10%, 10–14.9%, 15–19.9%, ≥20%
Coded QRISK2	<10%, 10–14.9%, 15–19.9%, ≥20%, missing
Systolic BP	<140, 140–159, ≥160, missing
Age	40–49, 50–59, 60–69, ≥70
Sex	Male, female
Ethnicity	White, Asian, black, other, missing
Townsend deprivation quintile	1st, 2nd, 3rd, 4th, 5th, missing
Urban/rural score	Urban, rural, missing
BMI	<20, 20–24.9, 25–29.9, 30–34.9, 35+, missing
Smoking status	Current smoker, ex-smoker, non-smoker, missing
Liver transaminases	Normal, abnormal, missing
Diabetes mellitus	Yes, no
Family history of CVD	Yes, no
Atrial fibrillation	Yes, no
Rheumatoid arthritis	Yes, no
Hypertension	Yes, no
Chronic kidney disease	Yes, no
HIV	Yes, no
Severe enduring mental illness*	Yes, no
Inflammatory conditions†	Yes, no
Antipsychotic medication	Yes, no
Long-term corticosteroids	Yes, no

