Immunosuppressant medication	Yes, no
Year quartile	1st, 2nd, 3rd, 4th

*Schizophrenia, bipolar affective disorder, mania or psychosis (unspecified), psychotic depression.

†Systemic lupus erythematosus, scleroderma, Bechet's syndrome, other inflammatory arthritis.

BMI, body mass index; BP, blood pressure; CVD, cardiovascular disease; HDL, high-density lipoprotein.

The potential cohort size can be estimated from the literature. Feasibility data from the THIN database identified over 360 000 patients over 2 years who were eligible for statin treatment for the primary prevention of CVD and had a lipid result and blood pressure coded on their medical record.^22^ Over a 5-year period we should expect to identify over double this number. Another cohort identified just over two million patients in the THIN database in the age range where NHS health checks are offered.^48^ Given that every patient who attends an NHS health check should have a lipid test undertaken and 20% of 40–75 years old are invited to have a health check each year, with ∼50% taking up this offer.^49^ This would generate around 200 000 coded lipid results in the target population annually.

The accuracy of the post hoc QRISK2 calculations will be tested through comparisons with corresponding coded QRISK2 scores in patients where these are available.

Additional modelling will also be undertaken to consider whether having a QRISK2 score coded on the medical record affects the probability of having a statin prescribed after adjustment for the level of CVD risk. Secondary analysis will also establish whether the threshold for initiating statins has changed over the course of the study period. The mean lipid levels and QRISK2 scores (both coded and calculated post hoc) of those initiated on statins and those not initiated on statins will be calculated each year to reveal any trends in the thresholds for initiation.

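### The 60-day leaving rule and the antihypertensive look-back are tied to the first lipid result although every later result is analysed, and results are accepted up to the end of 2016 without a guaranteed 60-day window

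*Protocol article*

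**What the plan says.** All references are to the protocol article.

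- **Index date (Population).** There is one per patient: "The date of the first coded lipid result in the study period will be considered the index date".
- **Unit of analysis (Exposure variables).** A patient can contribute several results: "each lipid result will be considered as a new exposure so long as it is not within 60 days of the last recorded lipid level". This is conditional on the exclusion criteria not being met.
- **Outcome (Outcome variables).** It is defined per result: "The outcome will be the prescription of a statin within 60 days of a set of lipid results".
- **Completeness of follow-up (Population).** The only rule is: "Patients will also be excluded if they left the database within 60 days of the index date".
- **Look-back (Predictor variables).** Treatment for hypertension means an antihypertensive prescription in the 180 days before the index date. Hypertension treatment is a listed QRISK2 input, and Table 1 carries a hypertension term.
- **Calendar limits (Population).** "The study period will run from the beginning of 2012 to the end of 2016". Patients stay eligible "until the earliest of the following dates: age 85, study end date, CVD diagnosis, other excluding diagnosis (as below), statin initiation" or a recorded contraindication. Practices must have data for the whole study period; nothing is said about data after it.
- **Use of calendar time (Analysis).** Mean lipids and QRISK2 scores of those started and not started on statins "will be calculated each year to reveal any trends in the thresholds for initiation". Seasonality is handled by "adding the year quarter as a variable in the model".

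**The concern.** There are two separate gaps.

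1. **Anchoring.** The unit of analysis is the lipid result, but two rules are attached to the patient's first result. A patient who leaves the database ten days after a third test is not caught by the leaving rule and stays in with an incomplete window. A patient first tested in early 2012 and retested in 2016 would carry hypertension-treatment status about four years old into both the calculated QRISK2 and the model.
2. **Study end.** Results are admissible up to the last day of 2016, yet each needs 60 days of prescription data. This does not stem from the index-date wording, since a first result in December 2016 has the same problem.

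If an incomplete window is counted as no prescription, the error runs one way, towards missed initiations. From the second gap it falls entirely in late 2016. That bears on the aim and second objective, which ask whether prescribing has changed over time.

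**Working it through.** **Plan's own figures.** The article gives no figure for incomplete windows. Its annual volume reproduces: 2 000 000 × 20% × 50% = 200 000 lipid results a year. Its minimum of 570 initiations also reproduces (10 × 57) and is not threatened by anything below.

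**Inputs from the article.** Study period 1 January 2012 to 31 December 2016 = 1827 days; outcome window 60 days.

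**Assumptions (not in the article).** Results are spread evenly over the calendar. Time from result to prescription is either uniform over 60 days or exponential with mean 7, 14 or 30 days, truncated at 60. Results with incomplete windows are kept and counted as not prescribed.

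**Step 1: results without a full window inside the study period.** 31 December 2016 minus 60 days = 1 November 2016, the last date with a full window. That leaves 2 November to 31 December, 60 days.

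- All results: 60/1827 = 3.3%, or about 33 000 of 1 000 000 at 200 000 a year.
- 2016: 60/366 = 16.4%.
- 2015–2016: 60/731 = 8.2%.
- Last quarter pooled over five years, as in Table 1: 60/(5 × 92) = 13.0%.

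**Step 2: share of initiations missed among those late results.** A result dated k days before study end loses 1 − F(k), where F(k) is the share of 60-day initiations made by day k. The mean loss is m = (1/60) Σ [1 − F(k)] for k = 0 to 59. For uniform timing F(k) = k/60. For exponential timing with mean μ, F(k) = (1 − e^(−k/μ)) / (1 − e^(−60/μ)).

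**Step 3: share of initiations missed = m × the share from step 1.**

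| Assumed timing | m | All initiations | 2016 | Pooled last quarter |
|---|---|---|---|---|
| Exponential, mean 7 days | 0.125 | 0.4% | 2.0% | 1.6% |
| Exponential, mean 14 days | 0.228 | 0.7% | 3.7% | 3.0% |
| Exponential, mean 30 days | 0.352 | 1.2% | 5.8% | 4.6% |
| Uniform | 0.508 | 1.7% | 8.3% | 6.6% |

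**Step 4: odds ratio for 2016 against earlier years with no true change.** With true rate p, the observed 2016 rate is q = p(1 − m × 0.164). For p = 10% and m = 0.5, q = 9.18% and the odds ratio is (0.0918/0.9082)/(0.10/0.90) = 0.91. Over p from 3% to 20% and m from 0.2 to 0.5, it runs from 0.97 to 0.90.

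**What cannot be sized.** Windows cut short because a patient left after a later test come on top of this. So does the effect of out-of-date hypertension treatment. The article gives neither a leaving rate nor the spacing of repeat tests.

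**The case against.** The case on the other side is substantial.

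- **The exclusions may already be re-checked.** The Exposure section admits a new result only if the exclusion criteria are not met, and leaving the database is worded as an exclusion. That may well be the intention. It does not settle the matter: the leaving rule is still measured from the index date, and the index date is explicitly the first result.
- **The look-back may be loose wording.** Predictor variables elsewhere calls for the most recent data up to QRISK2 coding or the end of the 60-day follow-up, so the index date may mean the start of each window. That is plausible, but the antihypertensive rule has its own explicit anchor, and an analyst following the text would freeze it.
- **Later prescriptions may be extracted.** The study end date limits eligibility, and the practice rule sets a minimum, not a data cut-off. A reader might infer that late results are scored as no statin. The article does not say so: it is silent on scoring and on prescriptions after 2016, so the losses above are conditional. The condensed format may explain the silence on extraction, but not the conflict over the index date.
- **The numbers are small.** This stands. A reader might take it that many results are affected; over the whole cohort it is about 3.3%. Looking at the last quarter of 2016 alone (60/92 = 65%) exaggerates, because Table 1 pools quarters over years.
- **Several analyses hardly move.** This also stands. The prescriber score compares counts of initiations above and below a total cholesterol of 6.5 mmol/L. Bias in the 2015–2016 scores does not follow unless time to prescription depends on cholesterol. Likewise, the yearly mean among those initiated is not shifted merely by losing initiations by date, and the non-initiated group gains only a few misplaced patients.

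**Conclusion.** The concern holds in limited form. The anchoring conflict is on the page and needs no assumption: one index date per patient, several analysed results per patient, and two rules that follow the former. The study-end gap is a separate omission. It affects 3.3% of results overall and 16.4% of those in 2016, assuming even testing. If the affected results are kept as not prescribed, 0.4% to 1.7% of all initiations and 2% to 8% of those in 2016 are missed across the timings tried.

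The exposed quantities are the 2016 prescribing rate, comparisons over time that depend on it, and the pooled last-quarter term. The study-end gap is too small to alter the primary lipid and QRISK2 associations materially. It is worth correcting because the possible error has a known direction, falls in the final year of a study about change over time, and is cheap to remove.

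**What to change.** 1. Define the index date as the date of each qualifying lipid result.
2. State that the exclusions, the 180-day look-back and the 60-day registration requirement apply at each such date.
3. Close the study-end gap in one of two ways:
   - accept results only up to 1 November 2016, which drops 60 of 1827 days, about 3% of results, all from 2016; or
   - extract prescriptions for 60 days after study end, to 1 March 2017, which drops no results for lack of calendar time but requires practices to have data to that date.

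The cost is a change of wording and an extraction filter. No change to the regression model follows from this point.

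### The entry rule takes the earliest of five dates that include study start, so it cannot delay anyone's entry past study start, and the one-year registration run-in is lost

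*Protocol article*

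**What the plan says.** The Population section fixes entry with one sentence: "Patients will be eligible for inclusion from the earliest of the following dates: study start date, acceptable mortality reporting date", continuing with "Vision date plus 1 year, registration date plus 1 year (to ensure time for baseline data to be recorded), and age 40". It gives reasons for two of these dates. The mortality-reporting date is there as a standard "which ensures that patient deaths and deregistrations are being recorded consistently". The year after registration is there so that baseline information has time to reach the record.

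Exit uses the same operator: "until the earliest of the following dates: age 85, study end date, CVD diagnosis, other excluding diagnosis (as below), statin initiation", followed by recording of a statin contraindication.

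The same section sets further conditions separately:
- Age: "Patients will be eligible for inclusion if they are aged between 40 and 84 years inclusive".
- Study period: "The study period will run from the beginning of 2012 to the end of 2016", and the index date is the first lipid result coded within that period.
- Practices: only those with data for the whole study period are used.
- Prior treatment: "Patients must not have been prescribed a statin prior to the index date". Pre-existing cardiovascular disease and any past statin prescription are also exclusions.

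**The concern.** A set of start conditions that must all be satisfied is met only when the last of them is met. Taking the earliest date means that meeting any one condition is enough, and study start is met by everyone from the beginning of 2012. The run-in and data-quality dates then do nothing, although the sentence explains why they are wanted.

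The cohort is defined by the absence of things: no earlier statin and no earlier cardiovascular disease. Absence is only as reliable as the record behind it. The section on missing data says that comorbidities not recorded will be treated as not present, so an uncoded diagnosis in a new registrant would pass the exclusion without any flag. The outcome is any statin prescription within 60 days of a lipid result, so a continuing user whose earlier prescriptions are not on file could be counted as newly started. The number of earlier lipid results is a model predictor and would be too low where previous results are not on file.

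If continuing users did enter in this way, their cholesterol would already be lowered by treatment. They would add low-cholesterol initiations to the primary model, and to the group below 6.5 mmol/L in the clinician-level score. That bears on the study's main question, whether lipid levels or predicted risk drive initiation.

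**Working it through.** The plan states no figure to reproduce here; the check is date logic.

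**Inputs, all from Population.** S = study start, taken as 1 January 2012. M = acceptable mortality reporting date. V = Vision date plus one year. R = registration date plus one year. A = date of 40th birthday.

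**Rule as written.** Entry = min(S, M, V, R, A). Since S is in the list, entry ≤ S for every patient, whatever the other four dates are. None of M, V, R or A can move entry later than 1 January 2012.

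**Rule that fits the stated purposes.** Entry = max(S, M, V, R, A). Entry then falls after S whenever any of the other four dates does.

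**Illustration with assumed dates** (the article gives no patient-level dates). Let M = 1 January 2008, V = 1 January 2006, R = 1 June 2015 (so registration on 1 June 2014) and A = 1 March 2014.
- As written: min = 1 January 2006, which is six years before the study opens.
- With the latest date: max = 1 June 2015.

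A lipid test in July 2014, about a month after registration, falls in the study period at age 40. It passes the rule as written and fails the run-in.

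**Which of the five limits survive through other sentences of the section.**

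| Limit | Enforced elsewhere? |
|---|---|
| Study start | Yes: the index lipid result must fall in the study period |
| Age 40 | Yes: separate age criterion of 40 to 84 |
| Vision date plus one year | Partly: practices need data for the whole period, but the extra year is not required |
| Mortality-reporting date | Partly: the same requirement, but it does not state the recording standard |
| Registration date plus one year | No |

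So one limit is lost outright, two are weakened, and two are unaffected.

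**Exit.** A patient should leave at the first disqualifying event, so the minimum is the correct operator there.

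**Sample size.** The stated minimum is 10 × 57 = 570 initiations. It does not use the entry date and is unaffected.

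**The case against.** The best defence is that this is a slip of one word. The reasons given within the sentence make the intention plain, and a programmer familiar with such data might well code the latest date. That may be so, but the document cannot show which version was coded. The rule is stated explicitly and is not a detail that an article leaves to a fuller protocol, and nothing else in the article corrects it.

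Three stronger readings are tempting, and the document does not support them.

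- *A reader might infer that all five entry safeguards are lost.* Age and study start are enforced separately, and the two practice-level dates are partly covered.
- *A reader might infer that prior statin use and cardiovascular disease cannot be checked in new registrants.* Nothing says that their earlier coded history is unavailable. The stated reason for the run-in supports only that history may be less complete. The predictor section also takes data up to the coded QRISK2 date or the end of the 60-day follow-up, so risk factors recorded soon after registration would still be picked up.
- *A reader might infer that every continuing user's first prescription at a new practice becomes a false initiation.* Three things must coincide: the earlier use is not on file, the lipid test comes before the first recorded prescription, and that prescription follows within 60 days. If the prescription is recorded first, the rule that "Patients must not have been prescribed a statin prior to the index date" removes the patient.

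These objections limit the consequence. They do not rescue the sentence.

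**Conclusion.** The entry rule is wrong as written and contradicts its own stated purposes. That conclusion is certain, because it needs only the presence of study start in the list. It is an internal contradiction in the wording, probably a drafting error, and not a considered design choice.

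The practical consequence is confined to the registration run-in, which has no backup, and to the two incompletely covered practice-level dates. Some misclassification of prior statin users and of patients with cardiovascular disease is possible, as is undercounting of earlier lipid tests. Any resulting dilution of the lipid association is a plausible direction, not a demonstrated bias. The article gives no patient turnover, no share of existing statin users among new registrants and no initiation rate, so any percentage of false initiations would rest on assumption alone; none is offered here. The point deserves correction before analysis because it defines who enters the cohort and the literal rule could be coded.

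**What to change.** In the entry clause of Population, replace *earliest* with *latest* and keep the five listed dates unchanged. Leave *earliest* in the exit clause. Confirm that the extraction code takes the latest of the five dates. The index date is currently tied only to the study period, so it should also be read as the first lipid result on or after the corrected entry date; otherwise the run-in would still not apply to the first test.

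The cost is one word, a check of the code and a slightly smaller cohort. The loss should not threaten the sample size. The article expects more than double 360 000 eligible patients over five years, and 570 is about 0.08% of 720 000 (570 / 720 000 = 0.00079).
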